## Abstract

**Introduction:**

Gonadotropin-releasing hormone antagonist (GnRH-ant) protocol is widely used in the world for controlled ovarian hyperstimulation (COH). However, previous studies have shown that pregnancy outcomes of fresh embryo transfer with GnRH-ant protocol are not ideal. Current studies have demonstrated the value of growth hormone (GH) in improving the pregnancy outcome of elderly women and patients with diminished ovarian reserve, but no prospective studies have confirmed the efficacy of GH in fresh embryo transfer with GnRH-ant protocol, and its potential mechanism is still unclear. This study intends to evaluate the impact of GH on IVF/ICSI outcomes and endometrial receptivity of patients undergoing GnRH-ant protocol with fresh embryo transfer, and preliminarily explore the possible mechanism.

**Methods:**

We designed a randomized controlled trial of 120 infertile patients with normal ovarian response (NOR) who will undergo IVF/ICSI from April 2023 to April 2025, at Department of Reproductive Medicine, Tongji Hospital, Tongji Medical College, Huazhong University of Science and Technology. The patients will be divided into the depot gonadotropin-releasing hormone agonist (GnRH-a) protocol group, GnRH-ant protocol control group, and GnRH-ant protocol plus GH intervention group at a ratio of 1:1:1 by block randomization design. Patients will be followed on enrollment day, trigger day, embryo transfer day, 7 days after oocytes pick-up, 15 days after embryo transfer, 28 days after embryo transfer, and 12 weeks of gestation. The primary outcome is the ongoing pregnancy rate. Secondary outcomes include the gonadotropin dosage, duration of COH, endometrial thickness and pattern, luteinizing hormone, estradiol, progesterone level on trigger day, numbers of retrieved oocytes, high-quality embryo rate, biochemical pregnancy rate, clinical pregnancy rate, implantation rate, ectopic pregnancy rate, early miscarriage rate, multiple pregnancy rate and incidence of moderate and severe ovarian hyperstimulation syndrome. The endometrium of certain patients will be collected and tested for endometrial receptivity.

**Ethics and dissemination:**

The study was approved by the Ethics Committee of Tongji Hospital, Tongji Medical College, Huazhong University of Science and Technology [approval number: TJ-IRB20230236; approval date: February 10, 2023]. The research results will be presented at scientific/medical conferences and published in academic journals.

**Clinical trial registration:**

Chinese Clinical Trial Registry; identifier: ChiCTR2300069397.

## Introduction

1

With the rapid development of assisted reproductive technology (ART), seeking an efficient and safe ovarian stimulation protocol is the main pursuit of doctors worldwide. Gonadotropin-releasing hormone agonist (GnRH-a) protocol, gonadotropin-releasing hormone antagonist (GnRH-ant) protocol, progesterone primed ovarian stimulation (PPOS) protocol, and minimal ovarian stimulation protocol are commonly used worldwide. The GnRH-ant protocol has received global attention for its simplified treatment course, shortened treatment period, and low incidence of ovarian hyperstimulation syndrome (OHSS) (1, 2). In 2020, the European Society of Human Reproduction and Embryology (ESHRE) published guidelines for controlled ovarian hyperstimulation (COH), indicating that GnRH-ant protocol can be used as first-line treatment for patients with high, normal, or poor ovarian response (3). Considering the safety of COH, ESHRE guidelines strongly recommended GnRH-ant protocol as a prior treatment for normal ovarian response (NOR) patients (3, 4).

For patients with NOR, the ideal therapeutic goals are to reduce the duration of COH, shorten the time to live birth and improve the pregnancy rate of fresh embryo transfer (1). However, previous studies have demonstrated that pregnancy outcomes of fresh embryo transfer with GnRH-ant protocol are not ideal. A retrospective study involving 203,302 fresh embryo transfer IVF cycles revealed a significantly higher cycle cancellation rate and a significant lower implantation rate and clinical pregnancy rate on the GnRH-ant protocol compared with those on the GnRH-a protocol (5). Another retrospective study indicated that the clinical pregnancy rate and live birth rate of patients receiving fresh embryo transfer with GnRH-ant protocol were significantly lower than those of frozen embryo transfer (6).

In recent years, how to promote the pregnancy rate of fresh embryo transfer with GnRH-ant protocol has become a research hotspot. Several studies have shown that serum luteinizing hormone (LH) levels, progesterone levels, trigger methods, and the method of GnRH antagonist usage during COH are associated with adverse pregnancy outcomes, but there is still a lot of controversy (7–13).

Growth hormone (GH) is a single-chain polypeptide hormone secreted by the anterior pituitary eosinophilic cells, consisting of about 190 amino acids. It has been more than 30 years since GH was first reported to be applied in the field of ART in 1988 (14). Current studies have shown that GH can regulate primordial follicle development, improve ovarian response to gonadotropin (Gn), improve oocyte quality, improve oocyte and granulosa cell mitochondrial function and oxidative stress state, and thus improve the pregnancy outcome of elderly women and patients with poor ovarian response (POR) (15). A meta-analysis consisting of 15 randomized controlled trials (RCTs) involving 1448 patients with POR found that GH can significantly increase the live birth rate, clinical pregnancy rate, and the number of oocytes retrieved, while significantly reducing the cycle cancellation rate and Gn dosage (16). Expert consensus on clinical diagnosis and treatment of POR patients in China points out that GH is recommended during the ART process for patients with POR, low embryo quality, thin endometrium, and recurrent implantation failure (RIF) (17). The guidelines also explicitly suggest the possibility of GH in improving endometrial receptivity.

A recent meta-analysis involving 17 RCTs found that GH supplementation may benefit patients with POR by improving endometrial thickness, clinical pregnancy rate, and live birth rate (18). Some studies have also confirmed that GH can improve pregnancy outcomes for patients with thin endometrium and RIF (19, 20). Besides, a single-center retrospective study including 80 patients who received GH treatment for POR or low fertilization rate or low blastocyst formation rate in the previous cycle found that GH can significantly increase the endometrial thickness without significant side effects or untoward reaction (21). However, no prospective study has confirmed the efficacy of GH in fresh embryo transfer with GnRH-ant protocol, and its potential mechanism has not been studied. This study intends to enroll NOR patients receiving fresh embryo transfer with GnRH-ant protocol to evaluate whether GH supplementation can improve the pregnancy outcome of fresh embryo transfer, and preliminarily explore the possible mechanism.

## Methods and data analysis

2

### Study design

2.1

This is a pilot study of infertile patients with NOR who will undergo *in vitro* fertilization and embryo transfer (IVF-ET) or intracytoplasmic sperm injection (ICSI) at Department of Reproductive Medicine, Tongji Hospital, Tongji Medical College, Huazhong University of Science and Technology from April 2023 to April 2025. According to the sample size estimation, 120 patients would be expected to be recruited for this study.

The primary inclusion criteria are (1) female aged 20-35; (2) menstrual cycle is between 25 and 35 days; (3) the body mass index (BMI) is between 18.5 and 25kg/m^2^; (4) basal follicle-stimulating hormone (FSH)<10 IU/mL; (5) antral follicle count (AFC) is between 7 and 15 or anti-mullerian hormone (AMH) is between 1.1 and 4.0 ng/ml; (6) IVF or ICSI for the first time; (7) the cause of infertility is male infertility, tubal infertility or unexplained infertility.

The primary exclusion criteria are (1) AFC<7 or >15 and AMH<1.1ng/ml or >4ng/ml; (2) polycystic ovarian syndrome (PCOS) patient; (3) ovarian or fallopian tube diseases, such as ovarian tumor, untreated severe hydrosalpinx, endometriosis cyst, etc.; (4) abnormalities of uterus or uterine cavity, such as adenomyosis, uterine submucosal fibroids or intramural fibroids affecting uterine cavity, genital tract malformations, endometrial polyps, intrauterine adhesions, thin endometrium, etc.; (5) preimplantation genetic testing due to chromosomal abnormalities, recurrent implantation failure (RIF), recurrent spontaneous abortion (RSA), or monogenic genetic diseases, etc.; (6) ICSI due to asoospermia or extremely severe oligospermia, asthenospermia (the sperm concentration was < 1×10^6^/ml and the percentage of forward motility sperm was < 1%, and the total number of forward motility sperm after processing less than one million), specific teratospermia (e.g., round head spermia, macrocephalic spermia, headless spermia, and multiple malformations of sperm flagella) or testicular sperm aspiration (TESA) or percutaneous epididymal sperm aspiration (PESA); (7) Other system-related diseases, such as thyroid diseases, diabetes, adrenal disorders, uncontrolled and untreated chronic diseases, suffering from diseases that are not suitable for pregnancy, etc.; (8) GH contraindications, such as diabetes mellitus, severe systemic infection, active tumor, active intracranial injury, pregnancy, etc.; (9) Pretreatment of other drugs recently, such as oral contraceptives, coenzyme Q10, metformin, etc.; (10) patient in other clinical studies at the same time, or the researcher deems it inappropriate to participate in this study (**Table 1**). Participants will be divided into depot GnRH-a group, GnRH-ant control group, and GnRH-ant plus GH intervention group randomly. We will investigate whether GH affects pregnancy outcomes and endometrial receptivity in patients undergoing GnRH-ant protocol with fresh embryo transfer (**Figure 1**).

**Table 1 T1:** The inclusion and exclusion criteria for selecting the study participants.

Primary inclusion criteria	Primary exclusion criteria
• Aged 20-35	• AFC <7 or >15 and AMH <1.1ng/ml or >4ng/ml
• Menstrual cycle 25-35 days	• PCOS
• BMI 18.5-25kg/m^2^	• Ovarian or fallopian tube diseases (e.g. ovarian tumor, untreated severe hydrosalpinx, endometriosis cyst, etc.)
• Basal FSH<10 IU/mL AFC 7-15 or AMH 1.1-4.0 ng/ml	• Abnormalities of uterus or uterine cavity (e.g. adenomyosis, uterine submucosal fibroids or intramural fibroids affecting uterine cavity, genital tract malformations, endometrial polyps, intrauterine adhesions, thin endometrium, etc.)
• IVF/ICSI for the first time	• PGT
• Male infertility or tubal infertility or unexplained infertility	• Asoospermia or extremely severe oligospermia, asthenospermia or specific teratospermia or TESA/PESA
	• Other system-related diseases (e.g. thyroid diseases, diabetes, adrenal disorders, uncontrolled and untreated chronic diseases, suffering from diseases that are not suitable for pregnancy, etc.)
	GH contraindications (e.g. diabetes mellitus, severe systemic infection, active tumor, active intracranial injury, pregnancy, etc.)
	• Recent pretreatment of other drugs (e.g. oral contraceptives, coenzyme Q_10_, metformin, etc.)
	• Patient in other clinical studies at the same time, or the researcher deems it inappropriate to participate in this study

BMI, body mass index; FSH, follicle stimulating hormone; AFC, antral follicle count; AMH, anti-mullerian hormone; IVF-ET, in vitro fertilization and embryo transfer; ICSI, intracytoplasmic sperm injection; PCOS, polycystic ovarian syndrome; PGT, preimplantation genetic testing; TESA, testicular sperm aspiration; PESA, percutaneous epididymal sperm aspiration.

**Figure 1 f1:**
[figure not shown]
Flow chart of the study design.

### Procedures

2.2

Patients who meet the above criteria will voluntarily decide whether to participate in this study. Informed consent would be signed by the designated doctor and the patient. A total of 120 infertile patients would be enrolled. The patients would be divided into the depot GnRH-a protocol group, GnRH-ant protocol control group, and GnRH-ant protocol plus GH intervention group at a ratio of 1:1:1 by block randomization design. Considering the open-label design of this study, both the attending nurse and the patient would be informed of the intervention method, while the embryologist and laboratory technician would be unaware of the intervention method. Participants’ baseline characteristics would be acquired from the hospital information database, including age, body mass index, primary infertility/secondary infertility; infertility duration; cause of infertility, history of fertility treatment; past medical history; history of drug allergy; vital signs; physical examination; urine hCG test; electrocardiogram; basal FSH, LH, E2, PRL, T, P, AMH, AFC; blood routine; urine routine; blood biochemistry; coagulation function; blood type; hepatitis B, syphilis, HIV examination, etc. will also be recorded.

#### COH protocol

2.2.1

Each group received different treatments as follows:

##### Depot GnRH-a protocol group

2.2.1.1

The patient would be given a subcutaneous injection of 3.75mg leuprorelin (Biote Pharmaceutical, Beijing, China) or 3.75mg triptorelin (Dophereline^®^, Ipsen, France/Decapeptyl^®^, Ferring, Switzerland) after endometrial thickness was determined to be <5mm with no follicle growth by transvaginal ultrasonography (TVS) on day 2 of the previous menstrual cycle. Approximately 28 days after injection, the patient would be confirmed to have reached the pituitary down-regulation position (E2 ≤30pg/ml and LH ≤2IU/L). Recombinant follicle-stimulating hormone (rFSH, Genescience Pharmaceutical, Changchun, China) would be selected for COH. The initial dose would be selected by the attending doctor according to the patient’s age, BMI, and ovarian reserve, and the dosage would be 150-225IU per day. During COH, doctors are allowed to adjust the dosage of Gn according to the patient’s ovarian response, and the maximum daily dosage would not exceed 450IU. When patients have a slow ovarian response during COH, human menopausal gonadotropin (HMG) (Lizon Pharmaceutical, Zhuhai, China) is allowed, and the dosage is determined by the attending doctor. During COH, any other adjuvant drugs are not allowed. When patients have two dominant follicles ≥18mm or three follicles ≥17mm in diameter, they would be triggered with recombinant human chorionic gonadotropin (rhCG, Ovidrel^®^, Merck Serono, Germany).

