##### GnRH-ant protocol control group

2.2.1.2

COH would be performed by a fixed GnRH-ant protocol. The patients would receive COH from day 2 or 3 of menstruation. The selection and adjustment of Gn and the treatment of slow ovarian response would be the same as those in the depot GnRH-a protocol group. During COH, any other adjuvant drugs are not allowed. On the 5th or 6th day of COH, 0.25mg cetrorelix acetate (Cetrotide ^®^, Merck Serono, Germany) or ganirelix acetate (Orgalutran^®^, Organon, USA/QingLe^®^, CHIA TAI TIANQING, Lianyungang, China) would be injected subcutaneously into the trigger every day. rHCG (Ovidrel^®^, Merck Serono, Germany) trigger would be used if the patient is not at high risk for OHSS. If the patient is at high risk for OHSS (trigger day E2≥5000pg/ml or ≥18 follicles with a diameter larger than 14mm), 0.2mg GnRH-a (Decapeptyl^®^, Ferring, Switzerland) or HCG 2000IU combined with 0.2mg GnRH-a (Decapeptyl^®^, Ferring, Switzerland) would be used for trigger. Other medications are at the discretion of the attending doctor.

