#### Follow-up plan

2.2.5

Patients would be followed on enrollment day, trigger day, ET day, 7 days after OPU, 15 days after ET, 28 days after ET, and 12 weeks of gestation (**Table 3**).

**Table 3 T3:** Overview of follow-up during the study.

Time	Follow-up Information
• Enrollment day	Patient randomization, collection of baseline characteristics of the participants (age, body mass index, primary infertility/secondary infertility; infertility duration; cause of infertility, history of fertility treatment; past medical history; history of drug allergy; vital signs; physical examination; urine hCG test; electrocardiogram; basal FSH, LH, E2, PRL, T, P, AMH, AFC; blood routine; urine routine; blood biochemistry; coagulation function; blood type; hepatitis B, syphilis, HIV examination, etc.).
• Trigger day	LH, E2, P levels; TVS; GH medication records; rFSH medication record; GnRH-ant medication record; HMG medication record; rhCG or GnRH-a medication record; untoward reaction record.
• ET day	Oocytes status; embryo status; luteal support medication record; number and morphological evaluation of transferred embryos; untoward reaction record.
• 7 days after OPU	Blastocysts status, collection of endometrium samples; untoward reaction record.
• 15 days after ET	serum β-hCG levels; luteal support medication record; untoward reaction record.
• 28 days after ET	TVS; luteal support medication record; untoward reaction record.
• 12 weeks of gestation	Pregnancy outcomes (ongoing pregnancy rate or early miscarriage or ectopic pregnancy); untoward reaction record.

hCG, human chorionic gonadotropin; FSH, follicle stimulating hormone; LH, luteinizing hormone; E2, estradiol; PRL, prolactin; T, testosterone; P, progesterone; AMH, anti-mullerian hormone; AFC, antral follicle count; HIV, human immunodeficiency virus; TVS, transvaginal sonography; GH, growth hormone; HMG, human menopausal gonadotropin; OPU, oocytes pick-up; ET, embryo transfer.

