### Secondary outcomes

2.4

The secondary outcomes in this study include the Gn dosage, duration of COH, endometrial thickness and pattern, LH, E2, P level on trigger day, numbers of retrieved oocytes, high-quality embryo rate, biochemical pregnancy rate, clinical pregnancy rate, implantation rate, ectopic pregnancy rate, early miscarriage rate, multiple pregnancy rate and incidence of moderate and severe OHSS. The high-quality embryo was defined as embryos with 7-10 cells of 2PN origin and blastomere fragments ≤20% on day 3 after fertilization (22). Biochemical pregnancy was defined as a serum level of β-hCG of more than 10 mIU per milliliter (27). Clinical pregnancy was determined when at least one gestational sac was observed on TVS. Early miscarriage was defined as pregnancy loss before 12 weeks of gestation.

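### The starting rFSH dose is chosen by a doctor not listed as masked, apparently after allocation, so the Gn-dosage comparison can reflect prescriber expectation as well as GH

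*Protocol article*

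**What the plan says.** - **Who chooses the dose, and from what.** Section 2.2.1.1 leaves the choice to the doctor: "The initial dose would be selected by the attending doctor according to" three named characteristics. These are age, BMI and ovarian reserve, and the permitted range is 150-225 IU per day. No mapping from these inputs to a dose is given. Doctors may later adjust to response, up to 450 IU per day, and may add HMG for slow response at a dosage they determine.
- **Which arms.** Section 2.2.1.2 applies this to the antagonist control arm: "The selection and adjustment of Gn and the treatment of slow ovarian response would be the same". The comparison there is with the depot arm. Section 2.2.1.3 builds the GH arm on that control arm and starts GH together with stimulation.
- **Masking.** Section 2.2 calls the trial open-label and says that nurse and patient are told the arm. Of the masked roles it says: "while the embryologist and laboratory technician would be unaware of the intervention method". The attending doctor is in neither list.
- **Timing.** Table 3 puts this under enrollment day: "Patient randomization, collection of baseline characteristics of the participants".
- **Outcomes.** Section 2.4: "The secondary outcomes in this study include the Gn dosage, duration of COH". The number of oocytes retrieved is also on that list.
- **Prior belief.** The Introduction says GH can improve ovarian response to gonadotropin. It cites a meta-analysis in poor responders that found lower Gn dosage and more oocytes with GH.

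**The concern.** Gn dosage is an outcome that the prescriber partly sets. If the prescriber knows that a woman will receive GH and expects GH to strengthen the response, there is a reason to start lower within the permitted range. A lower mean Gn dosage in the GH arm could then come partly from that expectation and be reported as a gonadotropin-sparing effect of GH. The exposure is avoidable, because every stated input to the starting dose is known before allocation. It matters in a pilot because section 2.5 says the study is meant to give a first view of efficacy and variation, and the Discussion foresees larger trials if the hypothesis is confirmed.

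**Working it through.** The article gives no figure for Gn dosage beyond the permitted range. The sample-size estimate in section 2.5 concerns ongoing pregnancy and does not bear on this point. The check is therefore a reading of the sequence, followed by an illustration.

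**1. Does the doctor know the arm when choosing the dose?**
- The design is open-label, and only two laboratory roles are unaware of the arm.
- The doctor runs stimulation and is not named as masked. Knowledge of the arm is a strong inference, not a statement in the text.
- Randomisation is on enrollment day. When the dose is chosen is not stated. In the depot arm rFSH comes about 28 days after the allocated injection. In the antagonist arms it starts on menstrual day 2 or 3. Nothing says the dose is settled before the allocation is known.

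**2. What can a difference in starting dose mean?**
- GH starts with stimulation, so the starting dose is chosen before GH can act. Between the two GnRH-ant arms, a difference in starting dose is either chance or a consequence of knowing the arm.
- Later adjustment is different: it responds to ovarian response and may be part of a genuine GH effect on Gn dosage.

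**3. Size of a possible shift (illustration)**

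From the article: range width 225 − 150 = 75 IU per day, and 40 women per arm. Assumed: 9-10 stimulation days; 10-30% of the GH arm started 75 IU lower and kept there; total dose about 1,850 IU, close to mid-range for ten days (187.5 × 10 = 1,875 IU).

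- Per shifted woman: 75 × 9 = 675 IU to 75 × 10 = 750 IU.
- Arm mean, lower end: 675 × 0.10 = 67.5 IU, and 67.5 / 1,850 = 3.6%, about 4%.
- Arm mean, upper end: 750 × 0.30 = 225 IU, and 225 / 1,850 = 12.2%, about 12%.

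**4. Chance of a significant result with no GH effect (illustration)**

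For a mean shift Δ, standard deviation SD and n = 40 per arm, the chance of two-sided p < 0.05 is approximately Φ(Δ / (SD × √(2/40)) − 1.96), with √(2/40) = 0.2236. The SD is assumed to be 300-700 IU, and duration is 10 days.

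| Share shifted | Δ (IU) | SD 300 | SD 500 | SD 700 |
|---|---|---|---|---|
| 10% | 75 | 20% | 10% | 7% |
| 25% | 187.5 | 80% | 39% | 22% |

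Example: 187.5 / (300 × 0.2236) = 2.795, and Φ(2.795 − 1.96) = Φ(0.835) = 80%.

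Section 2.6 plans Bonferroni post-hoc tests. If these cover three pairs, 1.96 becomes 2.394, and the 25% row runs from Φ(2.795 − 2.394) = 66% at SD 300 to Φ(1.198 − 2.394) = 12% at SD 700.

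**The case against.** **The rule is bounded and common to all arms.** The range is narrow, three baseline criteria are named, and the same selection rule applies throughout. That limits the bias but does not remove it, since no mapping fixes the dose within the range.

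**The sequence is inferred.** The article does not name the doctor as informed and does not say when the dose is chosen. A condensed article may also leave the order of enrollment steps to the full protocol. This stands as a caution, and it is why the point is worded as apparent.

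**The motive is weaker than it may look.** The cited reduction in Gn dosage comes from poor responders, while this trial enrolls normal responders. Only the general statement about ovarian response is not limited in that way. This stands.

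**The illustration leans high.** It assumes that shifted women cross the whole range, all in one direction, and stay lower throughout. In-cycle adjustment could raise low starters. This stands: the upper figures are near a worst case.

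**Stronger readings that the documents do not support.**
- A reader might infer that the Gn-dosage result would show expectation instead of a GH effect. Both can contribute, and nothing shows that expectation would dominate.
- A reader might infer that oocyte number is biased in favour of GH. A lower start in the GH arm would tend to reduce yield and so mask a gain; the direction is uncertain.
- A reader might infer that ongoing pregnancy is biased. Trigger-day E2, progesterone and oocyte count do enter the cancellation criteria in Table 2, so a path exists, but the article gives no basis for its size or direction.

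**Conclusion.** The point holds for the Gn-dosage secondary outcome. As written, the plan lets a doctor who is not among the masked roles set the starting dose, apparently after allocation, from inputs that were available beforehand. A starting-dose difference between the two GnRH-ant arms beyond chance cannot be caused by GH, yet it counts towards Gn dosage. That comparison can therefore reflect prescriber expectation as well as GH.

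The size is unknown. The 4-12% shift and the error rates above rest on assumed duration, total dose, SD and share shifted, none of which is in the article. They show that a modest shift could matter with 40 women per arm, not that one will occur. The effect on oocyte number is of uncertain direction, and the effect on ongoing pregnancy is unknown. This is worth correcting because the correction is cheap, but it does not threaten the trial's main comparison on the evidence available.

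**What to change.** - For all 120 women, have the attending doctor record the intended starting rFSH dose, under the existing criteria, before the allocation is disclosed. It must cover everyone, because nobody knows the arm at that moment.
- Leave the doctor free to depart from it, and log each departure with its reason.
- Report intended and actual starting dose by arm. A between-arm difference in departures is the most direct sign of prescribing influenced by allocation. Table 3 already lists an rFSH medication record, so the intended dose should be the only new item.
- Adjust the Gn-dosage comparison between the two GnRH-ant arms for the pre-allocation intended dose. This mainly adds precision and handles chance imbalance; it does not remove bias from later departures.

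No dose, range or adjustment rule changes. The cost is one line on the enrollment form and a reordered step. In-cycle adjustment and HMG use remain unmasked, so the report should state that limit when interpreting Gn dosage.
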